### Blinding

Because this project is a needling treatment, the needling operator must be in direct contact with the patient, to whom blindness cannot be applied. However, blinding is implemented for all other personnel involved in the study (including patients, those who recorded and entered the observational indicators, and the data statisticians), who will be unaware of the specific grouping of patients. To guarantee a more effective execution of the blind approach, each patient will be treated individually as much as possible, minimizing the need for patients to discuss with each other about the acupuncture treatment method, their feelings during the acupuncture, and the effects of the treatment.

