**Methods and analysis:**

The protocol outlines a double-center, randomized, and controlled trial design where both patients and assessors are blinded to the intervention being administered. The duration of the trial’s therapeutic intervention will span 4 weeks, followed by a 2-month observation period for monitoring any subsequent effects or outcomes. The 124 qualified individuals will be randomly allocated in a balanced 1:1 ratio to either the EA group or the drug group. All variables will undergo evaluation at the start of the study (week 0, baseline), during the treatment period at weeks 2 and 4, and during the follow-up period at weeks 8 and 12. The primary outcome is the Visual Analog Scale (VAS). Secondary outcomes include the Brief pain inventory-Facial scale (BPI-Facial), Pittsburgh Sleep Quality Index Scale (PSQI), Self-rating depression scale (SDS), Hamilton depression scale (HAMD), and Quality of Life Rating Scale (SF-36). The occurrence of any adverse reactions will be monitored and assessed throughout the duration of the trial.

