## Method and analysis

### Study design

This research is structured as a randomized, parallel-group, controlled clinical trial with patient-evaluator blinding. Based on the inclusion and exclusion criteria, patients with PHN of the head and face who met the requirements will be selected as the test subjects and randomly assigned to the EA group or the drug group. The efficacy of the subjects in the EA group and the drug group will be observed before treatment, immediately after the first treatment, after 2 weeks of treatment, after 4 weeks of treatment, at 1-month follow-up after the end of treatment and at 2-month follow-up after the end of treatment, respectively. The trial design is summarized in Figure 1, and the trial schedule for enrollment, treatment, and assessment is shown in Table 1. The reporting framework for this protocol adheres to the rigorous Standards for Reporting Interventions in Clinical Trials of Acupuncture (STRICTA) (39) as well as the comprehensive guidelines outlined in the Standard Protocol Items: Recommendations for Interventional Trials (SPIRIT) (40), ensuring a thorough and transparent documentation of the study.

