### Intervention

Subjects will undergo either EA or pharmacotherapy. Both groups will receive treatment for a duration of 4 weeks, followed by a 8-week follow-up period.

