#### Medication group

In this group, participants undergo treatment through the oral ingestion of pregabalin capsules (specification: 75 mg*8 capsules, manufactured by Pfizer Pharmaceutical Co., Ltd.) only, 150 mg each time, twice a day, for 4 consecutive weeks.

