### Outcome measures

#### Primary outcome measure

The Visual Analog Scale (VAS) allows patients to self-assess the intensity of head and facial pain by marking a point on a graduated straight line, ranging from 0 (indicating no pain) to 10 (representing the worst intolerable pain), with higher scores indicating greater pain severity. To elaborate, a score of 0 signifies the absence of pain; scores ranging from 0 to 3 denote mild and manageable pain; scores between 4 and 6 indicate pain that interferes with sleep yet remains tolerable; while scores from 7 to 10 represent severe and intolerable pain that significantly disrupts sleep or other daily activities. It is the most widely utilized tool for evaluating subjective symptoms, particularly in measuring pain severity (42, 43).

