## Limitations

This study has limitations due to the inherent flaws in the blinded implementation of acupuncture clinical trials. Despite our efforts to minimize potential bias by keeping statisticians and assessors blinded, operator knowledge of grouping is indeed unavoidable due to the nature of electroacupuncture treatment. In addition, patients may disrupt the blinding due to differences in treatment modalities, which may introduce bias into the study results. To minimize the interference of blinding limitations on the trial results, we will evaluate the blinding of operators and patients at the end of the trial, including operator-knowledge of the grouping, patient-perceived differences in treatments, and other factors that bias the blinding, such as differences in communication between operators and patients in different groups. In the meantime, we have referred to the relevant literature on similar studies (59, 60), and if bias occurs, we will assess the possible impact of each source of bias on the study results to estimate the extent of potential placebo effects and other biases. It is hoped that future studies will have better ways to address these limitations, and we will continue to monitor this issue.

Additionally, patients are required to visit the clinic on a weekly basis for three acupuncture sessions, each treatment takes more than an hour, the cost of time is greatly increased, and it is not as convenient as taking medication at home. For patients who face difficulties in frequently visiting the clinic, patient-self electroacupuncture treatment can be considered under the supervision of trained medical professionals. This form of treatment offers advantages such as enhanced convenience and personalized adjustments, aiding patients in their long-term management and rehabilitation. However, it also poses challenges including operational risks, variations in efficacy, substantial training requirements, and regulatory difficulties (61, 62). In our future research, we will delve deeper into the potential benefits and challenges associated with patient-self electroacupuncture.

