## Conclusion

In summary, this research protocol is a multicenter, randomized controlled trial with blinding of both patients and assessors. The objectives are to evaluate the effectiveness and safety of EA compared with medication; and to clarify whether EA in the treatment of cephalo-facial PHN has a clear and stable advantage over oral pregabalin alone in terms of improvement in mood, quality of sleep, and quality of life. This finding will provide new scientific and effective ideas for the clinical treatment of PHN.

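### The protocol states that patients are blinded, but they receive either electroacupuncture or capsules with no sham or dummy, so the self-rated primary outcome is in effect open-label

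*Protocol article*

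**What the plan says.** Four parts of the protocol article claim blinded patients:

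- Abstract, Methods and analysis: "both patients and assessors are blinded to the intervention being administered".
- Study design: a "randomized, parallel-group, controlled clinical trial with patient-evaluator blinding".
- Blinding: "blinding is implemented for all other personnel involved in the study (including patients, those who recorded and entered the observational indicators", with the data statisticians also listed. Only the needling operator is excepted.
- Closing Conclusion: a "randomized controlled trial with blinding of both patients and assessors".

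The treatments are alternatives. Under Intervention, "Subjects will undergo either EA or pharmacotherapy". The Operation, EA parameters and Course of treatment sections describe needling of the face and limbs with current at an intensity the patient tolerates, 60 minutes a session, three sessions a week for four weeks. In the Medication group, "participants undergo treatment through the oral ingestion of pregabalin capsules", and that section says this is their only treatment.

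The primary outcome is the VAS, which "allows patients to self-assess the intensity of head and facial pain".

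Limitations concedes that "patients may disrupt the blinding due to differences in treatment modalities". It plans to evaluate the blinding of operators and patients at the end of the trial and, if bias occurs, to estimate the extent of potential placebo effects with reference to literature on similar studies.

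**The concern.** A patient cannot be unaware of having needles and current applied for an hour, or of swallowing capsules instead. The protocol nevertheless states patient blinding as a property of the trial.

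This matters because the patient supplies the primary outcome. Whatever expectation patients attach to needling or to a drug, and whatever they gain from repeated long contact with a therapist, enters the VAS together with any specific effect of the stimulation. Readers and evidence synthesists use the blinding label to judge that risk. If the trial is reported as patient-blinded, a difference on the VAS will be credited to electroacupuncture itself more firmly than the design allows.

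**Working it through.** The point is settled by setting the sections side by side. The protocol has no figure of its own to reproduce here.

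**1. Can the patient be unaware of the arm?** The electroacupuncture arm has 3 sessions × 4 weeks = 12 sessions, and 12 × 60 minutes = 12 hours of needle retention. The drug arm has capsules only. Neither arm receives an imitation of the other's treatment. The patient knows the arm from the first treatment.

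**2. Does the stated safeguard help?** The Blinding section offers one measure: treating patients individually where possible, so that they do not compare experiences. That limits what patients learn about others. It cannot hide a patient's own treatment.

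**3. Could electroacupuncture patients also be taking pregabalin?** The closing Conclusion compares electroacupuncture with oral pregabalin alone, which could be read that way. Even so, the drug arm still has no needling, and the answer to step 1 is the same.

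**4. Who rates each outcome?** (Primary and Secondary outcome measures)

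| Scale | Rated by |
|---|---|
| VAS (primary) | patient |
| BPI-Facial | patient |
| PSQI | patient |
| SDS | patient |
| SF-36 | patient |
| HAMD | trained clinician, by interview and observation |

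Five of six scales, namely the primary and four of the five secondary ones, come from a rater who knows the arm. A blinded person who collects the forms does not change who made the rating.

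**5. Who can still be blinded?** Randomization and allocation concealment assigns collection of the efficacy indicators to a person unaware of the groups, and Blinding adds data entry and statisticians. All of that is feasible. The HAMD rater can be kept unaware by intention, but interviews patients who know their arm. Safety indicators are different: Safety evaluation has the acupuncturist record them.

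**6. Illustration only, under an assumed bias.** Take the one explicit numerical endpoint, the proportion with VAS ≤ 2 at 4 weeks (Sample size estimation). Assume no true difference, a pregabalin rate p0 = 0.744 and an electroacupuncture rate p1 raised by expectation alone. With 62 per group and 20% dropout, n = 62 × 0.8 ≈ 50 per group. With p̄ = (p0 + p1)/2, the one-sided 2.5% rejection rate is

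Φ{ [ (p1 − p0)√n − 1.96√(2p̄(1 − p̄)) ] / √(p0(1 − p0) + p1(1 − p1)) }.

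- 10-point shift: p1 = 0.844, p̄ = 0.794. (0.1 × 7.071 − 1.96 × 0.572)/0.568 = −0.73, giving about 23%.
- 5-point shift: p1 = 0.794, p̄ = 0.769. (0.05 × 7.071 − 1.96 × 0.596)/0.595 = −1.37, giving about 8.5%.

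The shifts are assumptions; the documents give no basis for their size or direction. The figures show what an open-label design could do under such a bias. They do not measure the harm done by the wording.

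**The case against.** **The problem is already disclosed.** Limitations names only statisticians and assessors as those kept blinded, and warns that differing treatments may break patient blinding and bias the results. A careful reader is warned. But the warning describes an existing blind that might fail, when there was never one to fail, and the four statements elsewhere are left uncorrected.

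**A journal article condenses.** A full protocol could contain more detail. The point does not rest on an omission, however: the article describes both arms and asserts a property they exclude, and its statement that the drug arm takes capsules only leaves no room for an unmentioned sham.

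Several stronger readings are tempting and are not supported:

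- *All blinding claims are false.* Collectors of efficacy data, data entry staff and statisticians can be blinded. Only the patient part is plainly untrue, with the consequence that the self-rated scales gain no blinded assessment.
- *The trial needs a sham arm, or its false-positive rate is known to be inflated.* Comparison with pregabalin is a stated aim and a legitimate open comparison. The comparator is an established first-line drug with its own expectation, so even the direction of a net bias is not given.
- *HAMD can be offered as the one securely blinded outcome.* It is scored by interviewing patients who know their arm, and no safeguard against disclosure is described.
- *The end-of-trial check is pointless and any placebo assessment impossible.* The check also covers perceived treatment differences and operator–patient communication, which are worth having. The trial itself cannot estimate a placebo effect, but an assessment from external literature is not excluded.

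**Conclusion.** The concern holds as a false statement about the design. The claim of patient blinding in the abstract, Study design, Blinding and closing Conclusion contradicts the treatments as described. The primary VAS and four of the five secondary scales are in effect open-label.

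The consequence is for interpretation: the trial estimates the effect of the whole electroacupuncture package, including expectation and therapist contact, against pregabalin. It cannot separate the stimulation from the rest. The conclusion rests only on the treatments as written and on who completes each scale. It needs no assumption about the size of any expectation effect, and the resulting bias cannot be quantified from the documents.

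**What to change.** 1. In the abstract, Study design, Blinding and closing Conclusion, replace the claim with wording such as: 'open-label for patients and operators; collectors of efficacy data, HAMD rater and statistician intended to be blinded'.
2. State that the estimated contrast is the whole electroacupuncture package, including expectation and therapist contact, against pregabalin.
3. In Limitations, say that patients are not blinded, in place of saying that they may break the blind.
4. Recast the end-of-trial blinding check as an assessment of patient expectation and perceived treatment differences.
5. State that the trial has no internal estimate of the placebo effect, so that any such assessment rests on external evidence.

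The cost is wording and a less favourable blinding label. No arm, visit, outcome or patient is added, and the comparison stays as planned.

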### Intervention

Subjects will undergo either EA or pharmacotherapy. Both groups will receive treatment for a duration of 4 weeks, followed by a 8-week follow-up period.

### Shallow plexus acupuncture combined with EA

The patients’ needles are uniformly used Huatuo brand disposable acupuncture needles sourced from Suzhou Medical Supplies Factory Co., Ltd., with specifications of 0.18 × 25 mm (needles for local acupoints) and 0.25 × 40 mm (needles for distal acupoints); and electro-acupuncture instruments are uniformly used with Han’s Acupoint Nerve Stimulation Instrument (model HANS-200). Acupuncture treatment is operated by an acupuncturist above the level of attending, and care is taken to sterilize the operator’s hands before and after the treatment, as well as to disinfect the local skin.

#### Prescription for acupuncture treatment

The main local acupoints will be chosen to be Sibai (ST2), Xiaguan (ST7), Dicang (ST4), Cuanzhu (BL2) and a-shi point on the affected side. Select acupoints according to the branch of the lesion, for eye branch lesions, Tongziliao (GB1) will be selected; for maxillary branch lesions, Quanliao (SL18) will be selected; for mandibular branch lesions, Jiache (ST6) will be selected. The distal acupoints will be chosen bilaterally at Hegu (L14), Waiguan (TE5), Taichong (LR3), and Sanyinjiao (SP6). For the specific positioning of acupuncture points, refer to the 2006 National Standard (GB/T12346-2006) of the People’s Republic of China, “Names and Positioning of Acupoints.” Table 2 provides a concise overview of the acupoint locations employed in this trial.

**Table 2 tab2:** Indication and localization of acupoints for the management of PHN.

Acupoints	Location
Primary acupoints	
A Shi acupoints	A Shi points refer to the specific locations within the herpes zoster lesion that experience the most intense pain sensations.
Si Bai (ST2)	Si Bai is on the face, with the eye looking straight down and the pupil straight down, when the infraorbital foramen is in the depression.
Xia Guan (ST7)	Xia Guan is on the face, in the depression between the center of the lower edge of the zygomatic bone and the mandibular incision.
Di Cang (ST4)	Di Cang is on the face, and is located in the depression formed by the zygomatic arch and the mandibular incision.
Cuan Zhu (BL2)	Cuan Zhu is on the face, in the depression of the eyebrow, at the supraorbital notch.
Supplementary acupoints	
Tong Zi Liao (GB1)	Tong Zi Liao is on the face, next to the lateral canthus of the eye, when the outer edge of the orbit.
Quan Liao (SL18)	Quan Liao is on the face, when the outer canthus of the eye is straight down, in the depression of the lower edge of the zygomatic bone.
Jia Che (ST6)	Jia Che is on the cheek, about 1 horizontal finger in front of and above the angle of the lower jaw, when the biting muscle bulges when chewing, and the depression is pressed.
He Gu (L14)	He Gu is situated in the area between the first and second metacarpal bones, precisely at the midpoint along the radial (thumb-side) border of the second metacarpal bone.
Wai Guan (TE5)	Wai Guan is positioned on the line extending from Yangchi point to the tip of the elbow, located 2 cun above the transverse crease of the wrist, situated between the ulna and radius bones.
Tai Chong (LR3)	Tai Chong is on the dorsal side of the foot, in the depression just before the union of the first and second metatarsal bones.
San Yin Jiao (SP6)	San Yin Jiao is positioned on the inner side of the lower leg, 3 cun above the prominence on the inner ankle bone, located along the posterior edge of the medial aspect of the tibia bone.

#### Operation

The patient is laid down in a supine posture, the whole body is relaxed, and the facial skin is routinely sterilized. Local points along the head and face herpes zoster lesion branch with 0.18 × 25 mm millimeter needle series of shallow stabbing method row stabbing method. Localized points do not necessarily require a sense of “getting qi,” the needle should be performed lightly, do not touch the trigger point. The distal acupoints of L14 and TE5 can be stabbed directly with 0.25 × 40 mm millimeter needles (to a depth of 20–30 mm), and after the patient consciously feels localized soreness and distension (“getting qi”), twisting and lifting insertion and diarrhea can be performed 10 times. If the patient is in a period of persistent pain, the first acupuncture points in the distal tract (L14 and TE5 points) can be needled, applying a large twisting, lifting and inserting diarrhea, and then needling the local acupoints after the pain has been slightly relieved.

#### EA parameters

Han’s Acupoint Neurostimulator (model HANS-200) is selected, local acupoints are chosen as ST7 + SL18 or ST7 + ST6, and distal acupoints were chosen as L14 + TE5 connected to EA, with sparse and dense waveforms of 2/100 Hz, and the duration of the treatment is 60 min, and the current intensity is tolerated by the patient.

#### Course of treatment

The needles are retained for 60 min during each time, which occurs every other day, resulting in a treatment schedule of 3 times per week for 4 consecutive weeks, amounting to a total of 12 treatments.

#### Medication group

In this group, participants undergo treatment through the oral ingestion of pregabalin capsules (specification: 75 mg*8 capsules, manufactured by Pfizer Pharmaceutical Co., Ltd.) only, 150 mg each time, twice a day, for 4 consecutive weeks.

### Outcome measures

#### Primary outcome measure

The Visual Analog Scale (VAS) allows patients to self-assess the intensity of head and facial pain by marking a point on a graduated straight line, ranging from 0 (indicating no pain) to 10 (representing the worst intolerable pain), with higher scores indicating greater pain severity. To elaborate, a score of 0 signifies the absence of pain; scores ranging from 0 to 3 denote mild and manageable pain; scores between 4 and 6 indicate pain that interferes with sleep yet remains tolerable; while scores from 7 to 10 represent severe and intolerable pain that significantly disrupts sleep or other daily activities. It is the most widely utilized tool for evaluating subjective symptoms, particularly in measuring pain severity (42, 43).

#### Secondary outcome measures

Secondary outcome measures include the Brief pain inventory-Facial scale (BPI-Facial), Pittsburgh Sleep Quality Index Scale (PSQI), Self-rating depression scale (SDS), Hamilton depression scale (HAMD), and Quality of Life Rating Scale (SF-36).

The BPI-Facial is a specialized assessment tool tailored for facial pain, covering aspects such as pain intensity, frequency of episodes, duration, and the extent to which pain interferes with daily functions like eating, speaking, and emotional well-being. Its primary role is to quantitatively evaluate the severity of facial pain and its impact on patients’ quality of life, providing valuable reference for the diagnosis and treatment of facial pain-related conditions (36, 44). During administration, respondents rate each item based on their personal experiences (e.g., pain intensity is assessed using a 0–10 numerical rating scale). The composite scores enable a comprehensive assessment of facial pain in patients with postherpetic neuralgia of the head and face, with higher scores indicating more severe pain and greater disruption to quality of life.

The PSQI is a standardized self-rating questionnaire designed to assess sleep quality over the past month. It encompasses seven key dimensions, including sleep latency, sleep duration, sleep efficiency, and others. The scale quantifies subjective sleep experiences through 19 questions and is widely utilized in clinical and research settings for screening and evaluating sleep disorders (45). During administration, respondents independently complete the self-assessment items, with scores calculated for each of the seven components (ranging from 0 to 3 points per component). The total score ranges from 0 to 21, with higher scores indicating poorer sleep quality.

The SDS is a self-assessment tool designed to evaluate depressive states in adults, comprising 20 items that address depression-related symptoms such as low mood, diminished interest, sleep disturbances, and appetite changes. Its primary function is to rapidly screen for the presence and severity of depressive symptoms, providing valuable reference for clinical diagnosis and psychological evaluation (25). During administration, respondents rate each item based on their actual experiences over the past week using a 4-point Likert scale (1–4 points). The raw scores of all items are summed to obtain a total score, which is then converted into a standardized score to determine the level of depression (below 53: normal; 53–62: mild depression; 63–72: moderate depression; above 72: severe depression).

The HAMD is a widely used clinician-administered tool for assessing the severity of depressive symptoms (46). It is evaluated by trained professionals through patient interviews and clinical observations. The scale encompasses over 20 symptom domains, including depressed mood, feelings of guilt, suicidal ideation, sleep disturbances, loss of interest in work, psychomotor retardation, agitation, anxiety, and others, with each item rated on a 5-point Likert scale (0–4). Higher total scores indicate greater severity of depressive symptoms, with typical classifications as follows: below 7 points suggesting no depression, 7–17 points indicating mild depression, 18–24 points representing moderate depression, and scores above 24 denoting severe depression.

The SF-36 is a widely utilized generic self-administered questionnaire for assessing health-related quality of life (HRQoL). It comprises 36 items covering eight dimensions: physical functioning, role-physical, bodily pain, general health perceptions, vitality, social functioning, role-emotional, and mental health. Its primary purpose is to comprehensively evaluate an individual’s physiological, psychological, and social functional status, and it has been extensively applied in evaluating HRQoL and intervention outcomes among patients with postherpetic neuralgia (47, 48). During administration, respondents answer based on their actual conditions over the past 4 weeks. Scores for each dimension are calculated using standardized scoring algorithms and transformed into a 0–100 scale, with higher scores indicating better health status in that specific dimension.

Patients with PHN are usually plagued by chronic pain that can somewhat affect sleep and mood, thus sleep quality and mood state can in turn affect their pain intensity, therefore the PSQI, SDS, HAMD and SF-36 will be used to assess the participants’ mental status and sleep quality. Outcome Measures will be performed at the baseline (pre-treatment), the 2 week after intervention, the 4 week after intervention, the 1-month follow-up and the 2-month follow-up to evaluate the severity of the disease and the treatment effect.

